Pyrazinamide resistance – Isolated pyrazinamide resistance is extremely rare, except among *M. bovis* strains (*M. bovis* is characteristically resistant to pyrazinamide). Patients found to have confirmed pyrazinamide resistance or intolerance will be taken off their assigned study regimen and treated using an individualized regimen. Patients with pyrazinamide resistance or intolerance will not be included in the analysis of sputum culture conversion. Patients receiving study (intensive) phase therapy at the time of discontinuation of the study regimen will have a study visit at 2 weeks after discontinuation of the study regimen for assessment of delayed toxicity, and then will no longer be followed in the study. Patients receiving continuation phase therapy at the time of discontinuation will no longer be followed in the study.

Rifampin resistance, with or without resistance to other drugs – Patients having a rifampin-resistant isolate or rifampin intolerance will be taken off their assigned study regimen and treated using an individualized regimen. Patients with rifampin resistance or intolerance will not be included in the analysis of sputum culture conversion. Patients receiving study (intensive) phase therapy at the time of discontinuation of the study regimen will have a study visit at 2 weeks after discontinuation of the study regimen for assessment of delayed toxicity, and then will no longer be followed in the study. Patients receiving continuation phase therapy at the time of discontinuation will no longer be followed in the study.

Ethambutol resistance – Rates of ethambutol resistance are low in Uganda[110], Canada[111], and the United States[109]. The study regimen should be very active for a patient having an ethambutol-resistant isolate. These patients will be kept on their assigned study regimen and included in the analysis of sputum culture conversion.

Resistance to two or more drugs - Patients with resistance to any two or more of the study drugs, most likely isoniazid and ethambutol or pyrazinamide, will be taken off their assigned study regimen and treated with an individualized regimen at the discretion of the investigator. These patients will not be included in the analysis of sputum culture conversion. Patients receiving study (intensive) phase therapy at the time of discontinuation of the study regimen will have a study visit at 2 weeks after discontinuation of the study regimen for assessment of delayed toxicity, and then will no longer be followed in the study. Patients receiving continuation phase therapy at the time of discontinuation will no longer be followed in the study.

Resistance to a non-study drug, with or without isoniazid-resistance – Rates of resistance to streptomycin are relatively high (7-10%) and often associated with isoniazid-resistance. In that resistance to non-study drugs should not affect the activity of the study drugs, patients with isolates having resistance to non-study drugs will be kept on their assigned study regimen and included in the analysis of sputum culture conversion.

- 1. Study drug toxicity

Patients will be closely monitored for signs and symptoms of study drug toxicity. For all toxicities that are treatment-emergent and that require the study therapy to be temporarily or permanently discontinued, relevant clinical and laboratory tests will be obtained as clinically indicated and repeated as needed until final resolution or stabilization of the toxicity.

If a patient develops hepatic toxicity requiring study drug discontinuation, the following evaluation will be undertaken: assessment for history of injection or noninjection drug use, alcohol ingestion, use of other hepatotoxic drugs, and performance of serologic tests for viral hepatitis (IgM antibody for Hepatitis A, Hepatitis B surface antigen, IgM antibody to Hepatitis B core antigen, antibody to Hepatitis C).

All symptoms and laboratory findings will be graded according to severity using the modified National Cancer Institute Common Toxicity Criteria (Appendix E). For the purposes of this study, pregnancy will be reported on the Adverse Event Form. All pregnant patients will be taken off study therapy and treated using the ATS/IDSA/CDC guidelines for tuberculosis treatment during pregnancy. Women who become pregnant will continue to receive scheduled follow-up, not receive additional x-rays unless clinically indicated, and be classified as being on a non-study regimen. The outcome of the pregnancy will be reported on the Adverse Event Follow-up Form.

- 1. Adverse event reporting

An adverse experience is defined as any unintended or abnormal clinical observation that is not of benefit to the patient. The adverse experiences that must be reported on an Adverse Event Form include: pregnancy, new medical diagnosis, grade 3 or 4 toxicity (potentially medication-related or other causes), study drug discontinuation, medication side-effects that are grade 3 or 4, and serious adverse events (defined in next paragraph). At the time of enrollment, if the patient already has a medical diagnosis whose signs or symptoms worsen during the study to a Grade 3 or 4, this is an adverse event that must be reported.

A serious adverse event (SAE) is defined as any experience that is fatal or life-threatening, is persistently or significantly disabling (as determined by the principal investigator), requires inpatient hospitalization, or prolongation of hospitalization, is a congenital anomaly, or overdose of study drugs. Any Grade 4 toxicity is considered an SAE.

The study drugs are moxifloxacin, ethambutol, isoniazid, rifampin, and pyrazinamide. The most common adverse effects associated with the study drugs are specified in Section 2.2 - "Study Drugs". The investigator is responsible for monitoring all adverse events that are observed or reported during the study, regardless of whether they are related to study drugs.

The TB Trials Consortium (TBTC) adverse experience reporting system has been developed to ensure timely and accurate reporting of adverse experiences in order to monitor patient safety, to comply with Food and Drug Administration (FDA) regulations, and to disseminate information to investigators working with the study drugs. In accordance with the FDA’s Code of Federal Regulations, the sponsor of this clinical trial (CDC) and the participating investigators are responsible for reviewing all information relevant to the safety of the study drugs. Reporting and monitoring of SAEs is required to alert the FDA, sponsor, institutional review boards, and the clinical investigators of real and potential safety issues. **Any Serious Adverse Event (this includes any Grade 4 toxicity) must be reported to the CDC on an Adverse Event Report Form within 48 hours of the site's awareness of the event.**

The CDC DTBE will carefully review the Adverse Event Report and use this information to monitor the investigational drug's toxicity profile and patient safety. Those adverse events, which are serious, unexpected, and related to the study drug, must be reported by the CDC and to the FDA in the form of a written Safety Report. The responsible institutional review board should be notified as soon as possible of any serious or life-threatening adverse experiences.

- 1. Management of adverse events

In general, for grade 1 toxicities, the patient will be followed carefully and the study drugs will be continued. For grade 2 toxicities, the patient will be followed more carefully, with additional laboratory and/or clinic visits as necessary, and the study drugs temporarily held at the investigator's discretion. For any grade 3 toxicity that, in the principal investigator’s judgment is due to study drug(s), the causative study drug(s) should be held. The clinician should rule out other possible causes of the symptoms before discontinuing study medication. When possible, concomitant medications should be held first at the discretion of the principal investigator if he/she suspects they are contributing to the toxicity. Depending on the nature and severity of the toxicity, the degree to which it resolves, and/or the emergence of alternative explanations for the toxicity or the subject’s deterioration, the study drugs(s) may be restarted at the discretion of the investigator. For any recurring grade 3 or grade 4 toxicity, the study drugs should be temporarily held and may be permanently stopped at the discretion of the investigator.

Any patient with grade 4 renal, hepatic, cardiac or hematological toxicity will be immediately discontinued from study therapy. The laboratory test or clinical finding in question will be reassessed as soon as possible. The repeat test will guide management of the event as follows:

- If the repeat assessment shows toxicity of grade 3 or lower, and if the patient has continued to receive study drugs between the two testing dates, then the patient will be managed according to the appropriate toxicity level of the repeat test.
- If the repeat test shows toxicity of grade 3 or lower, and if the patient has not received study drugs between the two testing dates, then the patient will be managed at the discretion of the investigator with regard to the re-administration of study drugs, and otherwise according to the toxicity level of the repeat test.
- If the repeat test shows grade 4 toxicity, then the patient will be permanently discontinued from study medications. Further treatment of TB will be directed by the investigator on an individualized basis. The patient will continue to be followed for study monitoring purposes (as are other patients who make a permanent departure).

For other grade 4 toxicities, the study drugs will be temporarily held and may be restarted or permanently stopped at the discretion of the investigator. Toxicities graded 3 or 4 by the Common Toxicity Criteria and occurring during study therapy will be documented on the Adverse Event Form, according to the criteria described in the next three sections. The maximum level of toxicity reached will be clearly indicated.

- 1. Criteria for discontinuation of study drugs

Certain events or conditions may necessitate temporary or permanent discontinuation of the study medication. Patients who experience such events or conditions, however, will still be "on study" and will be followed until study completion. Any patient for whom the study medication is temporarily discontinued will be restarted on study medication as soon as possible. Study regimens will be discontinued and non-study regimens will be used with continued study followup for patients who fail to respond to study therapy either clinically and/or bacteriologically, for patients in whom treatment-emergent drug toxicity warrants discontinuation of study therapy, and for patients who become pregnant. If study drugs are permanently discontinued, further antituberculous therapy may be administered at the investigator's discretion. These patients will be followed in the study for a maximum of 6 months of TB treatment, according to the guidelines and time-points established in the protocol, starting from the date of initiation of Study 28 intensive phase treatment.

- 1. Criteria for temporary discontinuation of study therapy
- Development of a toxicity that, depending on its nature and severity, requires temporary discontinuation of the study medication until the toxicity resolves as indicated in the preceding toxicity management section.
- Development of another medical condition that makes the administration of the study drug inadvisable. The decision to temporarily discontinue the study medication in this situation will be at the investigator's discretion. The period during which the patient is off study medication will be as short as clinically possible.
  1. Criteria for permanent discontinuation of study therapy
- Development of a toxicity that warrants permanent discontinuation of any study drug (refer to section on “Management of Adverse Events”).
- The patient refuses further therapy.
- It is the investigator's judgment that it is no longer in the best interest of the patient to continue study therapy.
- Termination of the study.

If a patient refuses further therapy or withdraws consent for treatment under the protocol, the patient will be treated with a non-study regimen. If the patient has withdrawn consent, all follow-up will stop.

- 1. Unscheduled unblinding of study assignment

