### Toxicity

The total incidence of all adverse effects from isoniazid is approximately 5%, many of which do not require discontinuation of the drug. Peripheral neurotoxicity is dose dependent and it is uncommon (<0.2%) at conventional doses. The risk of peripheral neuritis increases for persons who are malnourished or predisposed to neuritis by other illnesses. Concomitant administration of pyridoxine (vitamin B6) is recommended for these persons, and will be given to all patients in this trial. Other nervous system reactions are rare at normal doses, and they include convulsions, encephalopathy, optic neuritis, memory impairment, and psychosis. Gastrointestinal adverse effects include nausea, vomiting, and epigastric distress.

Asymptomatic elevation of aminotransferases is common and occurs in 10-20% of persons receiving isoniazid. However, idiosyncratic severe hepatic reactions are uncommon but are more likely in older persons (up to 2.3% hepatitis incidence in persons more than 50 years old), and may be life threatening. Daily consumption of alcohol increases the risk of isoniazid-associated hepatotoxicity by approximately four-fold. The risk of isoniazid-induced hepatotoxicity may also be increased in the postpartum period. The prodromal symptoms of hepatotoxicity are anorexia, nausea, vomiting, fatigue, malaise, and weakness; persons who take isoniazid and have these symptoms should stop therapy and be evaluated immediately.

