# METHODOLOGY

- 1. Study Design – 4-drug phase

This is a prospective randomized trial comparing two regimens for treatment of smear-positive pulmonary TB. Patients will be randomized to receive one of the two regimens listed below. All doses of study medications will be given as directly observed therapy.

**Table 13.** Intensive Phase Study Regimens

| **Study Regimen** | **Intensive phase (first 8 weeks of anti-TB therapy)** | |
| --- | --- | --- |
| Control regimen | HRZE daily* (+ moxifloxacin placebo)† |  |
| Moxifloxacin regimen | MRZE daily* (+ isoniazid placebo) † |  |

H – Isoniazid, R – rifampin, Z – pyrazinamide, E – ethambutol, M - moxifloxacin

* Daily therapy will be 5 days per week. However, at the discretion of the investigator, patients in either study arm may be given therapy 7 days per week during the first 2 weeks of the study (only 5 doses will be counted toward completion of the four-drug intensive phase of therapy).

† Vitamin B6 (50 mg) will be given with each dose of therapy

After completion of intensive phase therapy, patients in all study arms will then be treated for 18 weeks (30 weeks for those with cavitation on initial chest radiograph plus a positive sputum culture for *M. tuberculosis* at 2 months of therapy) with an ATS/IDSA/CDC-recommended continuation phase regimen.

Doses of study medications for the intensive phase are given below in Table 14. The duration of the intensive phase of therapy will be determined by the number of doses ingested, not by calendar time. Patients will complete the intensive phase when they have had 40 (5 days per week) directly-observed doses or 44 (7 days per week during the first two weeks then 5 days per week) directly-observed doses. To be eligible for inclusion in the analysis of culture-conversion, this therapy must have been completed within no less than 54 days and no more than 70 days.

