# Table 14. Doses of study medications during the intensive phase

| **Drug** | **Dose for daily therapy** |
| --- | --- |
| Moxifloxacin | 400 mg |
| Rifampin |  |
| < 45 kg | 450 mg |
| > 45 kg | 600 mg |
| Isoniazid | 300 mg |
| Pyrazinamide |  |
| < 40 kg | 25 mg/kg rounded to nearest 500 mg* |
| 40-55 kg | 1000 mg |
| > 55 kg - 75 kg | 1500 mg |
| > 75 kg - 90 kg | 2000 mg |
| > 90 kg | 2000 mg |
| Ethambutol |  |
| < 40 kg | 15 mg/kg rounded to nearest 100 mg |
| 40-55 kg | 800 mg |
| > 55 kg - 75 kg | 1200 mg |
| > 75 kg - 90 kg | 1600 mg |
| > 90 kg | 1600 mg |

* for pyrazinamide dosing in patients < 40 kg, 1000 mg typically used instead of 500 mg

Ethambutol may be discontinued if the patient’s *M. tuberculosis* isolate is susceptible to isoniazid, rifampin, pyrazinamide, and fluoroquinolones, as demonstrated by laboratory studies.

- 1. Continuation Phase Therapy

After completing the intensive phase of therapy, patients in all study arms will then be treated with an ATS/IDSA/CDC-recommended continuation-phase regimen. Recommended continuation-phase regimens that may be used include

- isoniazid + rifampin given daily [5 days/wk], thrice-weekly, or twice-weekly
- isoniazid + rifabutin for patients on medications having unacceptable drug-drug interactions with rifampin
- isoniazid + rifapentine once-weekly for HIV-seronegative patients with non-cavitary pulmonary disease plus a negative sputum smear at 2 months
- rifampin + pyrazinamide + ethambutol for patients who are intolerant of isoniazid (note: patients with known isoniazid intolerance cannot be enrolled in the protocol, but patients may develop isoniazid intolerance during study therapy).

The total duration of therapy will be 26 weeks (6 months) except that patients who have cavitation plus a positive sputum culture at the end of the intensive phase of therapy will receive a total of 38 weeks (9 months) of therapy.

- 1. Primary Objective
- To compare the culture-conversion rate at the end of the intensive phase of therapy of the moxifloxacin regimen vs. that of the isoniazid regimen
  1. Secondary Objectives

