### To compare the safety and tolerability of the moxifloxacin regimen to that of the isoniazid regimen

### To determine the time to culture-conversion of the moxifloxacin regimen and the isoniazid regimen using data from 2-, 4-, 6-, and 8-week cultures

- To compare the proportion of patients with any Grade 3 or 4 adverse reactions
- To compare adverse events and 2-month culture conversion rates among HIV-infected patients vs. HIV-uninfected patients
- To compare the rates of treatment failure of the moxifloxacin regimen and the isoniazid regimen
- To determine whether there is delayed toxicity attributable to moxifloxacin (toxicity that becomes evident after the 8 weeks of moxifloxacin therapy)
  1. Study Endpoints

**Sputum culture conversion** – sputum culture obtained at the end of the intensive phase of therapy has no growth of *M. tuberculosis*. The end of the intensive phase of therapy will be defined by completion of the required number of directly-observed doses (as defined in Section 3.1), rather than by a specific number of weeks of therapy. In order to assure that each subject will be evaluable for the primary endpoint, two sputum cultures will be obtained at the end of the intensive phase of therapy. These two cultures must have been obtained (a) 0-7 days after the completion of the intensive phase of therapy (preferably, one on the day of completion and one within 7 days of completion), and (b) prior to receiving more than one dose of continuation phase therapy. Sputum culture conversion will be based on the results of both sputum cultures performed at the end of the intensive phase of therapy.  **Both sputum cultures, if evaluable, should be negative for *M. tuberculosis* in order to conclude that sputum culture conversion was achieved.** Sputum cultures that are overgrown by bacteria and/or yeast will be considered unevaluable. Subjects who are unable to produce a specimen for sputum culture despite an attempt with sputum induction will be considered to have had a negative culture on that date.

**Safety and tolerability endpoints** – the primary endpoint for the analysis of safety and tolerability will be the proportion of patients who discontinue the assigned study regimen for any reason. Other aspects of safety and tolerability that will be assessed as secondary endpoints include mortality, the occurrence of Grade 3 and 4 toxicities and the rate and types of toxicity thought related to study drug by the investigator.

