End of intensive phase study visit –As above, the end of the intensive phase of therapy is defined by number of doses (40 to 44 doses, as defined in Section 3.1). When a patient has completed the assigned intensive phase, the monitoring blood tests will be obtained (complete blood count and serum AST, total bilirubin, and creatinine). Visual acuity and color vision testing, per standard site practice, will be repeated. In addition, two sputum cultures will be obtained for assessment of the sputum culture conversion, the primary endpoint of the trial. These specimens must be obtained on the day of completing the intensive phase of therapy or up to one week after completion, but before more than one dose of continuation therapy has been given. The two sputum specimens can be obtained on the same day.

- - 1. Study visits – continuation phase of therapy

Month 3 – Patients will have an assessment for delayed toxicity from the intensive phase of therapy. This will consist of a symptom-driven examination, visual acuity and color vision testing per standard site practice, and laboratory testing (complete blood count and serum AST, total bilirubin, and serum creatinine). A sputum specimen will be obtained for culture.

Months 4 through 6 (4 through 9 for those with extended therapy) - Patients will have study visits monthly during the continuation phase of therapy. Sputum cultures will be obtained at each study visit during the continuation phase of therapy until there have been 2 consecutive negative cultures. Laboratory testing, other than sputum cultures, will be at the discretion of the principal investigator. The study will end upon completion of 18 weeks (or 30 weeks for individuals with cavitation on initial chest radiograph plus positive sputum culture at 2 months of treatment) of an ATS/IDSA/CDC continuation phase therapy regimen and a related study visit. At each study visit during the continuation phase of therapy, patients will be asked about what medications they have been taking and if they have had any illnesses since the last visit.

- - 1. Scheduled unblinding of study treatment regimens

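### Delayed toxicity is defined only as toxicity appearing after the 8 weeks of moxifloxacin, which is when that arm usually starts its first in-study isoniazid, so shared toxicities cannot be attributed to moxifloxacin

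*Protocol*

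**What the plan says.** Section 3.4 (Secondary Objectives) sets the aim "To determine whether there is delayed toxicity attributable to moxifloxacin (toxicity that becomes evident after the 8 weeks of moxifloxacin therapy"). The Protocol Synopsis has the same aim with 2 months in place of 8 weeks. Neither gives a criterion other than when the toxicity appears.

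In the intensive phase (Section 3.1, Table 13) the experimental arm takes "MRZE daily* (+ isoniazid placebo") and the control arm "HRZE daily* (+ moxifloxacin placebo").

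Under Section 3.2, "patients in all study arms will then be treated with an ATS/IDSA/CDC-recommended continuation-phase regimen". The first listed option is "isoniazid + rifampin given daily [5 days/wk], thrice-weekly, or twice-weekly". Two more pair isoniazid with rifabutin or rifapentine. The only isoniazid-free option is "rifampin + pyrazinamide + ethambutol for patients who are intolerant of isoniazid".

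Section 4.1.4 places the check at month 3: "Patients will have an assessment for delayed toxicity from the intensive phase of therapy". It consists of a symptom-driven examination, visual acuity and colour vision tests, blood count, AST, bilirubin and creatinine. Later laboratory tests, other than sputum cultures, are left to the investigator.

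**The concern.** The objective asks a causal question about one drug, but the period it points to is one in which the arms differ in two ways. One arm has recently stopped moxifloxacin, and that same arm is usually also new to isoniazid. Randomisation protects a comparison of the two sequences. It does not separate the two components within the sequence.

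The protocol itself treats isoniazid as a cause of the events that month 3 is equipped to find. Section 2.2 states: "Asymptomatic elevation of aminotransferases is common and occurs in 10-20% of persons receiving isoniazid". It also lists gastrointestinal effects and severe hepatic reactions, and Section 5.9 names isoniazid hepatitis as a possible reason to unblind. At stake is a late safety signal recorded against moxifloxacin in a Phase 2 trial meant to support Phase 3, when the trial cannot tell it from the ordinary start of isoniazid.

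**Working it through.** The protocol gives no rate, sample size or power for delayed toxicity, so there is no figure to reproduce. The check traces exposure by arm and period.

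| Period | Moxifloxacin arm | Control arm |
|---|---|---|
| Intensive phase, about 8 weeks | moxifloxacin; isoniazid placebo | isoniazid; moxifloxacin placebo |
| Continuation phase | recent moxifloxacin; usually new to isoniazid | no moxifloxacin; isoniazid usually continued |

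1. *Coincidence of the two changes.* Three of the four continuation options contain isoniazid, and the fourth is for intolerance. Most moxifloxacin-arm patients therefore start isoniazid as moxifloxacin ends. Here first means first in the study, since entry allows up to 7 days of earlier multidrug therapy.

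2. *Where month 3 falls.* The Synopsis places this laboratory draw at week 12, and 12 − 8 = 4 weeks into continuation. For patients whose intensive phase took the 54 to 70 days required for the culture analysis, and assuming continuation starts at once, the interval is 84 − 70 = 14 to 84 − 54 = 30 days. It is the only scheduled safety laboratory draw after the switch.

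3. *Prior selection in controls.* By then controls have had 8 weeks of isoniazid, and some who could not tolerate it will have been identified or taken off it. The moxifloxacin arm has had no such period.

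4. *Does investigator judgement separate the drugs?* Section 3.5 records toxicity that the investigator thinks related to study drug, but Section 5.4 counts both moxifloxacin and isoniazid as study drugs. Sites normally stay blinded until four months after the last patient finishes continuation (Section 4.1.5), so they cannot tell who is new to isoniazid.

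5. *Direction, by illustration only.* Suppose moxifloxacin has no delayed effect. Take 205 per arm (all randomised) and the roughly 5% overall isoniazid adverse-effect rate in Section 2.2. Three things are assumed and are not in the protocol: that the whole 5% appears after week 8 in new users, a 2% background in both arms, and controls still showing a fraction f of the 5%.
   - Moxifloxacin arm: 205 × (0.02 + 0.05) = 14.4 expected cases.
   - Control: 205 × 0.02 = 4.1 (f = 0) to 205 × (0.02 + 0.025) = 9.2 (f = 0.5).
   - Chance of a nominally significant excess = Φ[(d − 1.96·SE₀)/SE₁], where d is the difference in rates, SE₀ the pooled and SE₁ the unpooled standard error. For f = 0: (0.050 − 1.96 × 0.02048)/0.02033 = 0.49, giving 69%. For f = 0.5: (0.025 − 1.96 × 0.02299)/0.02296 = −0.87, giving 19%. The nominal rate in this direction is 2.5%.

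The spread from 19% to 69% comes entirely from f. The illustration shows which way the contrast leans, not how far.

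**The case against.** The strongest reply is that the objective only asks whether such toxicity exists, that its parenthesis describes timing, and that investigator causality is also collected. A reader might infer that every late event will be charged to moxifloxacin. No section says so. Nor does Section 6.1 define a between-arm test of month-3 events; classification and tabulation may sit in a statistical analysis plan not shown here. That part stands, and the criticism is confined to the objective as worded. It is still more than a missing detail: the protocol names a target of attribution that its design cannot identify for shared toxicities, and no later tabulation rule changes that.

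Second, much of a remedy may already be available. The objective on Grade 3 or 4 reactions carries no 8-week limit, adverse events are collected to month 6 or 9 (Appendix D), and all randomised patients enter the toxicity analyses. This also stands. It makes the repair cheap, but the protocol does not say that this comparison runs from randomisation across the switch.

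Third, month 3 also includes vision tests and an examination, and the protocol notes tendon rupture even months after a fluoroquinolone is stopped. The objective therefore remains informative for tendon events. Retinal events are less clear: optic neuritis is listed as a rare isoniazid reaction, and both arms take ethambutol.

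**Conclusion.** The point holds for toxicities that moxifloxacin and isoniazid share, mainly hepatic, rash and gastrointestinal. A between-arm excess at or after month 3 reflects the sequence and cannot be assigned to moxifloxacin. This rests on most patients receiving an isoniazid-containing continuation regimen, which the listed options make likely but do not guarantee.

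Its size cannot be derived from the protocol. A reader might multiply the 10-20% aminotransferase figure by the number of patients entering continuation to obtain a count of spurious cases. The text does not support this. The figure is for asymptomatic elevation of any grade and has no time frame, whereas adverse-event reporting centres on Grade 3-4, and Grade 3 AST means more than 5 times the upper limit of normal (Appendix E). Neuropathy is also a poor example, at under 0.2% with pyridoxine given to everyone.

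A reader might go further and infer that the trial's safety conclusions are compromised. They are not. The primary tolerability endpoint, discontinuation in the first 2 months, precedes the switch. The within-8-week comparison is unaffected, and the randomised comparison of whole sequences remains valid.

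**What to change.** 1. Reword the objective, in the Synopsis and Section 3.4, as late toxicity of the treatment sequence: MRZE then continuation versus HRZE then continuation.
2. State that the Grade 3-4 comparison is cumulative from randomisation, through month 3 and through end of therapy, so that both arms' first in-study isoniazid exposure lies inside the window. Both cut-offs are needed. By week 12 controls have had about 12 weeks of isoniazid and the moxifloxacin arm about 4; by the end of 26-week therapy the figures are about 26 and 18.
3. Tabulate hepatic events after week 8 by arm and by time since first in-study isoniazid dose, with the end-of-intensive-phase bloods as reference. Label the table descriptive and non-randomised. Record the continuation start date; the protocol does not say that this is done, although the rule on sputum timing implies that it is known.
4. Keep moxifloxacin-specific attribution for pre-listed events such as tendinopathy. Retinal events should not be on that list. Restricting attribution to events before the first continuation isoniazid dose would not help, because continuation can follow almost at once and the window would be nearly empty.

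The cost is a narrower claim for one secondary objective, one recorded date and one extra table. No regimen or visit changes.
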